### Data collection

The following data will be systematically collected for all enrolled patients: (1) date of diagnosis and/or date of first HCC visit; (2) demographic and clinical characteristics at the time of diagnosis/first HCC visit and at all occurrences of new treatment intervention during the study period via medical chart review; (3) data on variants of HCC diagnosis, for example, mixed HCC, fibrolamellar HCC, and on the additional diagnosis of cholangiocarcinoma; (4) data on the use of currently available HCC treatment approaches during the study period from medical chart review; (5) data on the use of new treatments for HCC if they become available and are used prior to study end; (6) data on hospitalizations, clinical visits, and visits to other health care professionals, with collection of hepatic function, tumor assessments, and laboratory values according to clinical judgment; and (7) data on method of payment for health care utilization. All data will be collected retrospectively and prospectively at study sites in order to account for patient records over the full duration of the study; data collection is expected to be complete by June 2012. All sites will enter data into an electronic data capture system developed by Outcome Sciences, Inc. (Cambridge, MA, USA). Outcome Sciences will manage the data system, including monthly data monitoring and cleaning, site queries, and check of invalid clinical values determined a priori by study investigators. All data collection procedures will comply with Chinese privacy and confidentiality requirements.

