**Secondary end points**
Disease progression
Number of patients by treatment intervention with MRI/CT evidence of visible arterial enhancement, radiologic report of progression, or radiologic report of new tumor growth or symptomatic/clinical progression.
Time to disease progression
Number of days from date of treatment initiation to date of documented disease recurrence based on MRI or CT by treatment intervention, or symptomatic/clinical progression. Patients without recurrence will be censored from last date of treatment assessment.
Complication rate
Number of patients by treatment intervention who were withdrawn due to adverse events prior to introduction of other therapy.
Time to treatment-limiting adverse events
Number of days from first date of treatment to date of withdrawal due to adverse event(s) prior to introduction of other therapy. Patients without treatment-limiting adverse events will be censored at last date of treatment assessment.
Treatment failure rate
Number of patients by treatment intervention with a finding of treatment switch, HCC-related hospitalization and emergency room visit, disease recurrence, or death prior to introduction of other therapy.
Time to treatment failure
Number of days to first treatment failure overall and by individual item. Patients without treatment failure will be censored from last date of treatment assessment.

CT, computed tomography; MRI, magnetic resonance imaging.

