### Data analysis

To evaluate therapeutic approaches to HCC in China, the number and percentage of patients using each treatment (plus any new treatments that are approved and used within the study period) will be determined for each study year, in total and stratified by disease stage and site. Treatment patterns will also be assessed by disease stage for each study year. Patient characteristics will be stratified by disease stage and by site for each study year.

To assess therapeutic outcomes, age- and gender-adjusted rates will be calculated for each study end point. Cox proportional hazard models will be used for the time-to-event end points (overall survival and disease progression) to determine hazard ratios for each treatment approach, and Kaplan-Meier curves will be generated. Logistic regression models will be used for categorical end points (treatment-limiting adverse events and treatment failure). Covariates for the models will include disease stage, gender, age, duration of disease, etiology of disease, liver status, tumor size/spread, surgical intervention/number of interventions, and number of comorbidities; analyses will be conducted at the site and country level. The same analysis plan will be adopted for the evaluation of survival and other clinical end points with sorafenib versus other therapies, except that "treatment" will be included as a covariate. Further analyses will be conducted to evaluate clinical characteristics and demographics of patients treated with sorafenib versus other treatments for HCC. In addition, data collected will be used to analyze additional aspects related to HCC epidemiology and management in China (Table 2). All tests of statistical significance will be carried out at the 0.05 level.

**Table 2 T2:** Additional aspects of HCC management for potential evaluation using data from the HCC BRIDGE China national study.

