The eventual findings of the HCC BRIDGE China national study will need to be considered in light of the study's strengths and weaknesses. The primary strengths of this study are (1) the large number of patients included; (2) the geographic representativeness of the included sites; and (3) the use of real-life clinical practice data. Additional strengths include the use of centralized data monitoring, cleaning, site queries, and checking of invalid clinical values, which will enhance the quality of the collected data, as well as the use of identified prognostic factors for HCC survival to control for population differences that may influence treatment outcomes. The main potential study limitations are (1) treatment comparisons are performed in patients without prospective randomization methodology; (2) both academic and nonacademic centers/hospitals are included, which may result in differing quality of medical care for enrolled patients; (3) data quality is dependent on the thoroughness of the clinician's documentation of medical history, treatment, and outcomes; and (4) data collection bias is possible since clinical assessments are not conducted at predefined time points, as in a clinical trial, but at times determined by clinicians and their patients.

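### The progression hazard ratio treats unscheduled scan dates as exact event times, so any difference in scan spacing between treatments or periods would bias it

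*Protocol article*

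**What the plan says.** Four places in the protocol article bear on this point.

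- **Data collection.** Clinical encounters are recorded with "collection of hepatic function, tumor assessments, and laboratory values according to clinical judgment". No imaging schedule is set.
- **Table 1, Time to disease progression.** The clock runs from treatment initiation to the "date of documented disease recurrence based on MRI or CT by treatment intervention, or symptomatic/clinical progression". On censoring: "Patients without recurrence will be censored from last date of treatment assessment".
- **Data analysis.** "Cox proportional hazard models will be used for the time-to-event end points (overall survival and disease progression"), and their purpose is "to determine hazard ratios for each treatment approach, and Kaplan-Meier curves will be generated". On adjustment: "Covariates for the models will include disease stage, gender, age, duration of disease, etiology of disease, liver status, tumor size/spread". The rest of the list covers surgical intervention or number of interventions, and comorbidities. Nothing in it measures how often a patient was assessed. The same plan applies to sorafenib versus other therapies, with treatment added as a covariate.
- **Discussion, fourth limitation.** Data collection bias is conceded as possible because "clinical assessments are not conducted at predefined time points, as in a clinical trial, but at times determined by clinicians and their patients".

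**The concern.** Radiologic progression is not observed when it happens. It is known only to lie between the last scan without it and the first scan with it. Using the second date as the event time adds a delay that grows with the gap between scans. If the gaps are alike in the groups compared, the delay is shared and the hazard ratio is hardly touched. If one group is scanned more often, its progressions are recorded sooner and its hazard looks higher even when the disease behaves identically.

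Several planned contrasts could bring in such a difference: procedures against continuing drug therapy, sorafenib patients against historic controls from an earlier period, and pooled data from academic and nonacademic centers. The listed covariates are prognostic or treatment-history factors and do not stand in for scan spacing. At stake is a treatment difference in progression, tested at the 0.05 level, that is partly a difference in follow-up practice. A larger sample would not dilute such a bias; it would only make it more significant.

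**Working it through.** **Inputs.** From the article: unscheduled assessment (Data collection); event and censoring dates (Table 1); Cox model, covariates and the 0.05 level (Data analysis; two-sided assumed). The article gives no scan interval, median time to progression, effect size or power for this end point, so there is no figure to reproduce. Every interval, median and symptom share below is an assumption.

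**Step 1: closed-form check.** Let true progression be exponential with median *m* months, so λ = ln 2 / *m*, and let scans fall every *d* months. The first scan after progression then has mean time

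E(*d*) = *d* / (1 − e^(−λ*d*)).

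Without censoring, events per patient-month equal 1/E(*d*), so the false rate ratio of the more-scanned to the less-scanned group is E(longer *d*) / E(shorter *d*).

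- *m* = 4, λ = 0.1733, true mean 1/λ = 5.77. E(2) = 2/(1 − 0.7071) = 6.83 and E(4) = 4/(1 − 0.5) = 8.00; ratio 8.00/6.83 = 1.17.
- *m* = 4. E(3) = 3/(1 − 0.5946) = 7.40 and E(6) = 6/(1 − 0.3536) = 9.28; ratio 9.28/7.40 = 1.25.
- *m* = 12, λ = 0.0578. E(2) = 2/(1 − 0.8909) = 18.33 and E(4) = 4/(1 − 0.7937) = 19.39; ratio 19.39/18.33 = 1.06.

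The true ratio is 1 in each case. The bias grows with the scan interval relative to the time to progression.

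**Step 2: simulation of the Cox analysis.** Two treatments with the same true progression, 500 patients each, 200 replicates, scan intervals jittered by ±25%, events dated to the first scan after progression, and censoring at the last scan before a uniform 6-36 month cut-off. Hazard ratios are more-scanned against less-scanned, with all progression found by scan:

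| Scan intervals (months) | Median 4 | Median 6 | Median 12 |
|---|---|---|---|
| Equal | 0.99-1.01 | 0.99-1.01 | 0.99-1.01 |
| 2 v 3 | 1.10 | 1.06 | 1.03 |
| 2 v 4 | 1.21 | 1.14 | 1.07 |
| 3 v 6 | 1.37 | 1.21 | 1.09 |

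The false-positive rate at 0.05 was 80%, 46% and 12% for 2 v 4 months, and 100%, 80% and 18% for 3 v 6 months (medians 4, 6 and 12). These rates belong to the assumed 500 per group and would rise in larger groups.

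A different set-up (8000 per group, ±0.5 month jitter, censoring at 36 months) gave 1.22 and 1.35 at a median of 4 months, 1.10 and 1.19 at 6, and 1.04 and 1.14 at 9, for 2 v 4 and 3 v 6 months respectively. The direction is stable; the second decimal is not.

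**Step 3: allow for symptomatic progression.** Table 1 counts it as an event. For the twofold spacing differences, the false hazard ratio is 1.04-1.24 when 30% of progressions can be found earlier through symptoms, and 1.00-1.14 when 60% can. These ranges also depend on how soon symptoms are assumed to follow progression.

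**Step 4: check the remedy.** An interval-censored Weibull proportional hazards model fitted to the same kind of data (2 v 4 and 3 v 6 months) gave 1.00-1.01 when all progression was scan-detected, and 0.94-0.98 with 30% symptom-detected. Most of the bias goes. A smaller one in the opposite direction remains when symptoms drive detection.

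**The case against.** The strongest reply is that the article already discloses unscheduled assessment as a limitation, that Cox regression is a conventional choice for progression, and that interval-censored sensitivity analyses and tables of scan intervals are commonly left to a statistical analysis plan, which is not shown. The absence of such detail is indeed no fault in a condensed article. What stands is that this article itself fixes the event date, the model and the covariates, and that this combination does not deal with the limitation it concedes. The Discussion does not connect that limitation to the progression hazard ratio.

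A reader might go further and infer that progression is dated only by scan, or that the planned hazard ratios do measure imaging frequency. The article supports neither. Table 1 also counts symptomatic/clinical progression, which weakens the effect and can bring it to nil. No section reports scan spacing by treatment, site or period, or says that it differs, so the bias is conditional. The larger figures also assume twofold spacing, short medians and scan-only detection; 2 v 3 months gives 1.03-1.10. With resection, transplantation and ablation among the treatments, one short median need not represent the cohort.

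It is also fair to say that replacing the Cox model outright would be hard to defend. Interval censoring assumes that scan times are unrelated to the disease state, which is doubtful when clinicians and patients choose them. Site-level analyses, which are planned, deal with part of any between-site difference, though not with differences between treatments within a site.

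**Conclusion.** The concern holds in a conditional form. As stated, the analysis yields a biased progression hazard ratio wherever assessment spacing differs between the groups compared, and nothing in the listed model would reveal or correct this. Under the assumed intervals and medians, the false hazard ratio is about 1.03-1.37 if all progression is found by scan, and about 1.00-1.24 for twofold spacing differences if 30-60% is found by symptoms. The actual size is unknown until spacing is tabulated, and it may be negligible if spacing is similar, progression is slow or symptoms dominate detection.

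The reach is limited to a secondary end point. Overall survival, the primary end point, has death as its event, and that date does not depend on imaging. The change is worth making, but the study's main result does not hang on it.

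**What to change.** In Data analysis:

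1. Report the median interval between tumour assessments by treatment, site and period (2005-2007 and 2008-2011), so that readers can see whether the condition for bias is met.
2. Keep the Cox model and add an interval-censored proportional hazards (or Weibull) analysis with the same covariates. Place radiologic progression between the last scan without it and the first scan with it, and keep exact dates for symptomatic progression.
3. State in advance that a difference in progression between treatments will not be concluded unless the two analyses agree.

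Tumour assessments are already among the data collected, so the main cost is analysis time. There are three drawbacks. Confidence intervals will be somewhat wider. The method needs the dates of negative scans, which the article does not say are always recorded and which depend on clinicians' documentation. Some bias will remain where symptoms trigger scans (hazard ratio 0.94-0.98 with 30% symptom-detected progression in the check above), which is why the second analysis should stand beside the Cox model and not replace it.

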### Sample size

Sample size requirements for the Chinese regional sites are approximately 200 patients per site per year between 2008 and 2010 (plus approximately 192 per site for the first 6 months of 2011) to capture current treatment and clinical outcomes in HCC, and 100 patients per site between 2005 and 2007 for historic controls. Pooling of data across all sites in China will be employed to describe disease and treatment characteristics across the country.

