### Patients

All patients enrolled in the HCC BRIDGE study must meet 3 key inclusion criteria: (1) diagnosed with HCC between January 1, 2005, and June 30, 2011, in accordance with American Association for the Study of Liver Diseases/European Association for the Study of the Liver guidelines [11]; (2) aged at least 18 years at the time of HCC diagnosis; and (3) received or receiving treatment for HCC through a site enrolled in the HCC BRIDGE trial. Patients participating in other clinical trials will be included in the study if the patient is enrolled in a single-arm clinical trial, enrolled in a randomized clinical trial of HCC adjuvant therapy, or was not selected to receive active treatment in a randomized clinical trial that was conducted between 2005 and 2007. Any patient whose first active HCC-directed treatment is received via participation in a randomized clinical trial of primary HCC therapy will be excluded from the current study, since this treatment regimen would have been determined by a study protocol rather than by the treating physician. Similarly, patients included in the China national study who subsequently enroll in such a trial will be censored from the study at that time point. Patients with unknown month and year of HCC diagnosis or of the first visit at the site of inclusion will be excluded. Furthermore, to preserve regional representation within China, patients who reside outside the province of interest for a particular study site will also be excluded. Finally, in order to avoid selection bias when the number of eligible patients at a site exceeds the number allowed according to study sample size calculations, an enrollment scheme will be adopted such that the same number of consecutive patients are enrolled each month. For example, in the first year of data entry, if a site is to enroll 200 patients, approximately 17 consecutive patients diagnosed with HCC will be enrolled in each month. If there are less than the specified numbers of patients in any given month, we ask that the corresponding number of extra patients be enrolled in the following month.

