## Results

The number of patients enrolled across the various geographic regions captured in the global HCC BRIDGE study is expected to exceed 20,000. For the HCC BRIDGE China national study, a total of 15 sites across China have been selected for inclusion at the time of writing. At present, the anticipated country-wide study population is approximately 9000 patients (Figure 1).

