## Discussion

Over the past 3 to 4 decades, China has experienced a substantial increase in the incidence of HCC [5], and the country now accounts for more than half of the world's cases of this malignancy [2,3]. Nevertheless, in spite of the huge health care burden of HCC in China, there has never been a truly geographically representative study of HCC in this country and active surveillance is currently lacking. This suggests that the current estimates of the incidence and prevalence of HCC in China may not be accurate, and that regions with a current high unmet need and/or a high risk for new HCC cases may be unidentified.

The HCC BRIDGE China national study is the first geographically representative epidemiologic study of HCC in China and is expected to include more than 9000 patients over its course. This study, via its inclusion of a large number of sites across all 7 traditional regions of China, will facilitate a thorough assessment of HCC patient characteristics, treatment allocation, and clinical outcomes, across the entire country, as well as allowing a unique analysis of possible regional variations in these aspects of HCC epidemiology and management. Ultimately, the study will help determine levels of unmet medical need and identify regions of high risk for HCC within China.

As well as contributing to the general understanding of treatment patterns and associated outcomes among HCC patients in China, the data generated by the HCC BRIDGE China national study may provide insights into other aspects of HCC epidemiology and management, such as the potential role of HCC screening in treatment allocation and outcomes, and possible differences in clinical outcomes among different HCC patient subpopulations. Moreover, the study data may further help address other unanswered questions related to HCC in China, including questions about the appropriateness of current standards of care for HCC, the extent of usage and the impact of traditional Chinese herbal medicine, and best practices in clinical care for Chinese patients with HCC. Through these investigations and analyses, the study also has the potential to inform ongoing China public health reform, policy, and practice.

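### The per-site requirements add up to 13,380 patients at the 15 selected sites, but the article anticipates about 9000 and does not explain the difference

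*Protocol article*

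**What the plan says.** The Sample size section of the protocol article sets its requirements per site and by period of diagnosis: "approximately 200 patients per site per year between 2008 and 2010 (plus approximately 192 per site for the first 6 months of 2011"), and "100 patients per site between 2005 and 2007 for historic controls".

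The Results section gives the number of sites, "a total of 15 sites across China have been selected for inclusion at the time of writing", and then the total: "At present, the anticipated country-wide study population is approximately 9000 patients". The Abstract repeats both figures. The Discussion words the total differently, saying that the study "is expected to include more than 9000 patients over its course".

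Three other places bear on the point.

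- **Study design and Patients:** diagnoses from January 2005 to June 2011 are eligible, so all three quota periods belong to the study population.
- **Patients:** where a site has more eligible patients than the sample size permits, a scheme applies under which "the same number of consecutive patients are enrolled each month". The example given is a site enrolling 200 in the first year of data entry, at about 17 per month.
- **Loss to follow-up:** deaths are expected to be unverifiable for 5% of patients, and the sample size is said to allow for this already.

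**The concern.** The article prints the components of the sample size, the number of sites and a total, and the total is not the product of the other figures. This is not a detail that a condensed article may leave to the full protocol, because both sides of the sum are on the page.

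The composition of the cohort is at stake more than its overall size. The Comparator groups section matches patients treated before sorafenib became available to sorafenib-treated patients on age, sex, Child-Pugh status and stage. The quotas supply 1,500 such historic patients. A reader who starts from 9000 cannot tell whether 1,500 or some smaller number is planned, nor how many patients come from 2011. The size of the cohort is also the first strength listed in the Discussion, so the total should be one that the plan supports.

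A second, separate oddity is the six-month quota for 2011, which is nearly a full year's quota for the years before it. Follow-up ends on December 31, 2011, so these patients can contribute at most 6 to 12 months from diagnosis to an overall survival end point.

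**Working it through.** **Inputs**

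| Quantity | Value | Source |
|---|---|---|
| Sites | 15 | Abstract; Results |
| 2008-2010 | 200 per site per year × 3 years = 600 | Sample size |
| First half of 2011 | 192 per site | Sample size |
| 2005-2007 historic controls | 100 per site | Sample size |
| Unverifiable deaths | 5% | Loss to follow-up |
| Anticipated total | about 9000 | Abstract; Results |

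No effect size, power or event count is given, so the check is a direct sum and not a power calculation.

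**Can the stated total be reproduced from the quotas?**

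Per site: 3 × 200 + 192 + 100 = 892.

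All sites: 15 × 892 = 13,380, made up of

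- historic controls, 15 × 100 = 1,500;
- 2008-2010, 15 × 600 = 9,000;
- first half of 2011, 15 × 192 = 2,880.

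Gap: 13,380 − 9,000 = 4,380, and 4,380 / 13,380 = 32.7%. Put the other way, 9000 / 892 = 10.1, so at full quota about 10 sites would supply 9000.

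**Does another reading give 9000?**

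| Reading | Per site | × 15 |
|---|---|---|
| All quotas as written | 892 | 13,380 |
| As written, multiplied by 0.95 | – | 12,711 |
| As written, divided by 0.95 | – | 14,084 |
| Historic 100 taken as per year | 1,092 | 16,380 |
| 2011 figure taken as 92 | 792 | 11,880 |
| 2011 figure taken as 96 | 796 | 11,940 |
| 2011 figure taken as 100 | 800 | 12,000 |
| 2008-2010 counted as two years, rest as written | 692 | 10,380 |
| 2008-2010 and historic controls, no 2011 | 700 | 10,500 |
| 2008-2010 and 2011, no historic controls | 792 | 11,880 |
| 2008-2010 only | 600 | **9,000** |
| Two years × 200, plus 100 for 2011, plus 100 historic | 600 | **9,000** |

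Only the last two rows reach 9000. The first of them drops two of the three periods. The second contradicts both the printed 192 and the three calendar years 2008, 2009 and 2010.

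**The 2011 quota**

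192 / 6 = 32 per month, against 200 / 12 = 16.7 per month at the annual quota, a ratio of 1.92. Within the 2008-2011 quota the 2011 patients make up 192 / 792 = 24%. At a constant monthly rate they would make up 100 / 700 = 14%.

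**The case against.** The strongest reply is that the two figures are different things. The quotas are targets, while 9000 is a forecast given as of the time of writing. The Patients section treats the sample-size number as a ceiling, foresees months with too few patients, and excludes patients who live outside a site's province. A forecast below target is therefore possible. The Discussion's wording, read as a floor, does not conflict with 13,380 at all.

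Part of this stands. Under-recruitment cannot be ruled out, so the remedy must allow either figure to be the one restated. It does not remove the conflict. The Sample size section calls its numbers requirements, nothing in the article announces an expected shortfall, and one third is more than the word approximately can cover. The floor reading helps only the Discussion, since the Abstract and Results say about 9000.

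A reader might go further in three ways that the article does not support.

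- **That 9000 was obtained by omitting the historic controls and the 2011 patients.** This rests only on a numerical match. The article does not say how 9000 was derived.
- **That at 9000 there would be no historic-control group.** The Comparator groups and Sample size sections both keep that group, and any shortfall could be spread over all periods.
- **That 192 is a misprint for about 96 to 100.** The article gives 192 as a figure of its own, and no text says that the earlier rate must continue. The even-enrolment rule is not broken, because 192 over six months is an even 32 per month, and the example of 17 per month concerns the first year of data entry. Substituting 96 or 100 would not bring the total to 9000 either.

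The historic quota is also less ambiguous than it may look. The 200 is given per year and the 100 is not, so its plain reading is a total for 2005-2007.

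**Conclusion.** The point holds as an internal contradiction in a stated sample size. As written, the requirements come to 13,380 patients at 15 sites, and the anticipated total is 4,380 (33%) lower without explanation. This assumes 15 sites, three calendar years at 200, and a historic quota of 100 in total per site. A per-year reading of the 100 would widen the gap to 16,380 against 9000.

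The match of 9000 with 15 × 600 is a likely clue to where the figure came from, and no more than that. Nor is a loss of power or an effect on the primary analysis shown: the article gives no effect size or event count, and the analyses it describes do not use the total.

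The 2011 quota is a lesser, separate query. The higher monthly rate is a fact; whether it was intended cannot be told from the article. The 24% is a share of the 2008-2011 quota. It is not a share of the sorafenib era, because that era starts at each site's first recorded use of the drug. Short follow-up for 2011 diagnoses comes from the fixed cut-off date at any quota; a larger quota only raises the share of patients affected.

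**What to change.** Make the total and the quotas agree in the Abstract, Results and Discussion, in one of two ways.

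1. **If the quotas stand:** give the anticipated total by period. As written, and at the current 15 sites, that is 1,500 historic controls + 9,000 for 2008-2010 + 2,880 for the first half of 2011 = 13,380. Mark it as tied to the current number of sites.
2. **If about 9000 is the realistic yield:** say that it falls short of the stated requirements, and give the number expected in each period, including how many historic controls it delivers.

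Separately, confirm 192 for the first half of 2011 as an intended oversample, with the reason, or correct it to the number intended.

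The cost is a few restated figures and a sentence or two of explanation. Either the headline total or the quotas will change, or a shortfall will have to be disclosed. No extra enrolment and no change of design is needed.
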